#### Qualitative data collection

Longitudinal qualitative data will be collected throughout the project as portrayed in Fig. 3, including action plan interviews with local implementation teams, drop-in interviews with frontline staff, and focus group interviews, as described in Table 2. The researchers involved in qualitative data collection and analysis, who are also part of the implementation team, will seek to demonstrate *empathic neutrality* [29], for example by prefacing interviews with the fact that we are interested in learning about implementation experiences and that there are no right or wrong answers. In doing so, we hope to limit desirability bias in the information shared. Having three data collection activities will also allow for rigorous triangulation of findings among data sources and will all inform the ongoing formative evaluation (see Table 1).

**Table 2 Tab2:** Qualitative data collection methods

Data collection method	Participants	Description	Documentation
Action plan interviews	Local nvHAP ambassadors	Semi-structured interviews of approximately one hour to assess the current implementation status of each nvHAP bundle element throughout the study periods, as well as identify potential or actual barriers and facilitators to implementation, and plan a list of actions to be taken locally.	Interviews will be audio-recorded and transcribed where acceptable and structured notes will be taken systematically. These and the written action plan documents established after each interview will be included in qualitative analysis.
Drop-in interviews	Frontline clinicians	Short, semi-structured, drop-in interviews of 10–15 min to learn from frontline staff about their experience with the nvHAP implementation and identify local barriers and enablers to implementation.	Detailed, structured notes will be taken during and after each drop-in interview and/or the interview will be audio-recorded and transcribed verbatim to be included in qualitative analysis.
Focus group interview	Frontline clinicians	Semi-structured focus group interviews of approximately 1 h to assess implementation outcomes among frontline staff.	Focus groups will be audio-recorded and transcribed verbatim for inclusion in qualitative analysis.

For drop-in and focus groups interviews, participants will be purposefully sampled to include a representative mix of professions (nurses, physicians, and physiotherapists) from wards within the participating departments Given inconsistencies in definition and application of ‘saturation’ as a measure of sufficient sampling, ‘information power’ has been proposed as a concept to guide adequate sample size [30]. By having a clearly defined qualitative study aim, an information-rich sample of interview participants, guiding theoretical frameworks to inform structured data collection by skilled interviewers expert in the study topic, our study design and sampling strategy is designed to achieve high information power [30].

### Analysis

#### Quantitative analysis

##### Analyses of nvHAP bundle effectiveness

To evaluate the effectiveness of the intervention bundle, two distinct analyses are performed. First, a change point model will be combined with piecewise constant rates with additional sine-cosine waves to account for seasonality. Poisson regression (with log link function) is used to analyse the monthly overall nvHAP incidence rate over all departments, using the monthly sum of the nvHAP cases over all departments as “count” and the monthly sum of the number of patient days (in thousands) over all departments as offset. Study period on the hospital level (hospital baseline, implementation, intervention period) will be used as explanatory factor (see Additional file 6 ‘Statistical analysis’ for detailed statistical model). We may use a quasi-poisson model in case of overdispersion.

Second, a longitudinal Poisson regression will be used. The monthly number of nvHAP cases in each department will be modelled by a generalized estimating equation (GEE) with departments as clusters. This allows to account for the non-independence of consecutive nvHAP counts within departments, to model the temporal correlation structure (e.g. first order autoregressive) and to account for over-dispersion, if necessary. We will assume a Poisson error distribution for the nvHAP counts and use the log link function. As above, we may use a quasi-Poisson model in case of overdispersion. We will use a time-dependent, department-specific binary indicator variable for department-level implementation of the intervention bundle (possibly with an intermediate level for the implementation phase) as explanatory variable. Further, we will adjust for seasonality of nvHAP incidences by inclusion of sine/cosine waves.

Because the baseline period includes nvHAP rates from 2017 which served (inter alia) as basis for the choice of the nine departments, we will perform sensitivity analyses excluding data from 2017 for all analyses described above to assess a potential “regression to the mean” effect.

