#### Study population

All patients hospitalized in nine predefined medical and surgical departments and their corresponding wards will be included in this study. The nine departments were chosen based on the following criteria; 1) nvHAP rate above the 50th percentile according to UHZ nvHAP data from the year 2017; 2) high absolute number of patients with nvHAP according to UHZ nvHAP data from the year 2017; 3) organizational structure, e.g. departments sharing same nursing or medical personnel; 4) representing both medical and surgical specialties.

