#### Outcomes

##### Effectiveness outcomes

The primary outcome is nvHAP incidence rate, defined as the number of patients suffering from nvHAP per 1000 patient days per month. Secondary outcomes are in-hospital mortality rate; length of stay; and adherence to individual bundle elements and the nvHAP bundle as a whole.

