#### Study periods on department and hospital level

Baseline period will start at the same time for all departments and will be of different length (minimum 12 months) as implementation of nvHAP prevention measures will occur at the department level and the start of implementation activities is chosen by every department, primarily relying on availability of resources.

We define three study periods on the *department level*, 1) department baseline period, before implementation of nvHAP bundle in the specific department; 2) department implementation period, a two month time frame starting with the beginning of implementation activities in the respective department; 3) department intervention period following the department implementation period.

On the *hospital level* the three periods are defined as follows: 1) hospital baseline period, before starting implementation in the first department; 2) hospital implementation period, from the beginning of the implementation period of the first department until end of implementation period of the last included department; 3) hospital intervention period following the hospital implementation period. Figure 2 depicts an anticipated study timetable.

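### The hospital-level model has no adjustment for department mix, so if rates differ and patient-day shares drift between periods, the period effect could be confounded

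*Protocol article*

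**What the plan says.** The protocol article, under *Effectiveness outcomes*, takes the nvHAP incidence rate as primary outcome, "defined as the number of patients suffering from nvHAP per 1000 patient days per month". Under *Analyses of nvHAP bundle effectiveness* it describes two analyses.

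- **Hospital level.** A Poisson regression of the monthly case total over all departments, with "the monthly sum of the number of patient days (in thousands) over all departments as offset". On the regressors: "Study period on the hospital level (hospital baseline, implementation, intervention period) will be used as explanatory factor". Sine and cosine waves handle season, and quasi-Poisson is foreseen for overdispersion.
- **Department level.** "The monthly number of nvHAP cases in each department will be modelled by a generalized estimating equation (GEE) with departments as clusters". The stated covariates are a department-specific implementation indicator and seasonal waves. No department factor is stated.

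The one sensitivity analysis named there drops the 2017 data, to look for regression to the mean. Under *Study population*, departments were chosen on their 2017 rate, absolute case number, organisational structure and "representing both medical and surgical specialties". Additional file 6, which holds the detailed model, is not shown.

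**The concern.** Once cases and patient-days are summed, the model sees one rate per month, and that rate depends on which departments supplied the patient-days. Suppose that a high-rate department closes beds, or a low-rate department expands, between the hospital baseline and the hospital intervention period. The pooled rate then falls although every department performs as before, and the period factor records the fall as benefit. The opposite drift would hide a real benefit.

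Two features of the plan make this worth attention. There is no control group, as the *Discussion* acknowledges, so nothing outside the nine departments would reveal a drift. And the observation window is long enough for activity to change: the baseline includes 2017 and collection stopped at the end of February 2020, which is up to 38 months if it began in January 2017.

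**Working it through.** The article states no department rate, patient-day share or target effect, so there is no figure of its own to reproduce. The check is an identity with labelled assumptions, followed by a small simulation.

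**Identity.** With w_d the share of patient-days and r_d the rate of department d, pooled rate = Σ w_d·r_d. If no r_d changes, the pooled rate ratio between two periods is Σ w1_d·r_d / Σ w0_d·r_d. This equals 1 if all r_d are equal or the shares do not move. Moving a fraction s of all patient-days from one group of departments to another of the same size, spread evenly within each group, changes the pooled rate by s × (mean rate of receivers − mean rate of donors) / overall mean rate.

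**Assumptions.** Nine departments with equal baseline shares; rates evenly spaced on the log scale; s moved from the three highest-rate to the three lowest-rate departments. Pooled rate ratio with a true ratio of 1.00 in every department:

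| Highest/lowest rate | s = 2 points | s = 5 points | s = 10 points |
|---|---|---|---|
| 1 | 1.000 | 1.000 | 1.000 |
| 2 | 0.990 | 0.974 | 0.949 |
| 3 | 0.984 | 0.960 | 0.920 |
| 4 | 0.980 | 0.950 | 0.900 |
| 6 | 0.975 | 0.937 | 0.875 |

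Example for ratio 4 and s = 5 points: the lowest three average 0.601, the highest three 1.699, and all nine 1.103. So 0.05 × (0.601 − 1.699) / 1.103 = −0.050. Reversing the shift raises the rate by the same amount.

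**How extreme that alignment is.** Three of nine equal departments hold 33.3% of patient-days. A 5-point move therefore takes 5/33.3 = 15% of the donors' own days. There are 1,680 ways to move 5 points from any three departments to any other three. The absolute bias over all of them is:

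| Highest/lowest rate | Mean | Median | Maximum |
|---|---|---|---|
| 2 | 0.8% | 0.7% | 2.6% |
| 3 | 1.2% | 1.1% | 4.0% |
| 4 | 1.6% | 1.4% | 5.0% |

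The table of rate ratios above thus shows the maximum among three-to-three moves. Moving the 5 points from the single highest to the single lowest department gives 0.966, 0.946 and 0.932 for ratios 2, 3 and 4, but that department would lose 5/11.1 = 45% of its days.

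**Does the second analysis remove it?** Simulated data: rate ratio 3, 10-point shift in the intervention period, true ratio 1.00, 36 months, 60 data sets. The GEE fits assumed a patient-day offset and used the hospital period in place of the department-specific indicator, so they are illustrative.

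| Model | Estimated rate ratio |
|---|---|
| Summed hospital-level model | 0.918 |
| GEE, independence | 0.918 |
| GEE, AR(1) | 0.919 |
| GEE, exchangeable | 0.952 |
| Department-month Poisson with department factor | 0.997 |

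Fitted to noise-free expected counts, AR(1) and exchangeable both gave 0.96. How much of the mix effect a GEE without a department factor removes therefore depends on the working correlation. In these fits it never removed all of it.

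**The case against.** The strongest reply is that nothing in the article shows a change in mix. The nine departments are predefined, and "Baseline period will start at the same time for all departments", so staggered entry does not itself alter who contributes. Annual swings in mix would largely go into the seasonal terms, and irregular monthly ones mostly into overdispersion. Selecting departments with above-median rates may also narrow the spread. All of this stands, and it makes the concern conditional: only a sustained drift aligned with the hospital periods biases the estimate.

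A second reply is that the crude hospital rate is a legitimate quantity and is what the outcome definition describes. That also stands, and it argues for reporting an adjusted estimate beside the crude one. It does not make the crude period effect a clean measure of the bundle.

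A reader might go further and infer that the hospital-level analysis is confounded, or that a bias of about 5% is to be expected. The documents support neither, because they give no department rates, no shares and no sign of drift, and 5% is the least favourable three-to-three alignment at a four-fold spread. A reader might also suppose that the GEE already adjusts for departments. The article names them only as clusters.

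**Conclusion.** The concern holds as a conditional weakness. As stated, the hospital-level model cannot separate a change within departments from a change in the mix of departments. Neither the quasi-Poisson option, the exclusion of 2017, nor the GEE as described reliably does so. Additional file 6 could add a covariate for mix, but a department effect cannot be estimated from summed counts.

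The size is unknown. With equal baseline shares and rate ratios of 2 to 4, a 5-point shift gives about 1 to 2% typically and about 2.5 to 5% from the three highest-rate to the three lowest-rate departments, in either direction. Biases of 8 to 13% need a 10-point shift in that alignment and a spread of 3 to 6. This is modest, but it bears on one of the two effectiveness analyses of the primary outcome and can be removed with data that the second analysis already needs.

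**What to change.** Add a mix-adjusted estimate of the hospital-period effect, by either route:

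1. **Department-month model.** Fit department-month counts with department intercepts, each department's log patient-days as offset, the same period factor and the same sine/cosine terms. Use standard errors that allow for overdispersion and for serial correlation within departments; clustering by month alone would not cover the latter.
2. **Expected-cases offset.** Keep the summed model, but use as offset the log of Σ (baseline rate of department d × its patient-days that month). A uniform true ratio of 0.70 then returns Σ 0.70·r_d·PD_d / Σ r_d·PD_d = 0.70 under any mix (PD_d being department d's patient-days), and with a constant mix the rate ratio equals the planned one. Baseline rates are treated as known and would include the 2017 data used for selection, so repeat it with weights that exclude 2017.

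The two routes are not identical when the mix changes, because the intercepts in the first draw on all periods and the weights in the second on baseline only. Name one in advance. Report it beside the crude pooled rate ratio, at least as a prespecified sensitivity analysis, with patient-day shares by department and period so that readers can see whether the mix moved.

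The cost is slightly more analysis work and no new data. The adjusted figure is a mix-adjusted rate ratio and no longer describes the crude hospital rate. Drift in case mix inside a department would remain.

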##### Analyses of process indicators

To portray adherence to the single prevention measures and the nvHAP bundle as a whole a descriptive analysis will be performed, summarizing continuous and intermittent process indicators and the ‘nvHAP overall adherence score’ by department-level periods. Further, we will evaluate whether the process indicators are associated with the nvHAP incidence rate. We will use GEEs with Poisson error and departments as clusters (as described above) to model the monthly nvHAP rates as dependent on either single continuous process indicators or on all continuous process indicators combined.

To model monthly nvHAP as dependent on intermittent process indicators (either single process indicators, all process indicators combined, or the nvHAP overall adherence score), we will use GEEs with Poisson error and departments as clusters (as described above). Because the intermittently collected process indicators are collected only at four time points, we will use linear interpolation to derive monthly values for these process indicators.

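### The department-level and process-indicator GEEs rest on nine clusters with no stated small-sample correction; the usual robust z-test would run at about 9% to 14% instead of 5%

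*Protocol article*

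**What the plan says.** The Study population section fixes the number of clusters: "All patients hospitalized in nine predefined medical and surgical departments and their corresponding wards will be included in this study".

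The section on analyses of nvHAP bundle effectiveness gives two analyses. The first is a hospital-level Poisson regression on monthly totals over all departments. The second is the one at issue: "The monthly number of nvHAP cases in each department will be modelled by a generalized estimating equation (GEE) with departments as clusters". The stated reasons for the GEE include being able "to model the temporal correlation structure (e.g. first order autoregressive) and to account for over-dispersion, if necessary". The error model is given as "We will assume a Poisson error distribution for the nvHAP counts and use the log link function", and the exposure as "We will use a time-dependent, department-specific binary indicator variable for department-level implementation of the intervention bundle", possibly with an intermediate level for the implementation phase. Sine and cosine terms are added for seasonality.

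The section on analyses of process indicators reuses this GEE "to model the monthly nvHAP rates as dependent on either single continuous process indicators or on all continuous process indicators combined". It does the same for the intermittent indicators, taken singly, combined, or as the overall adherence score.

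The article names no variance estimator, small-sample correction, reference distribution or significance level for these models. The limitations in the Discussion do not mention the small number of clusters. They do rely on the department-level results, alongside the hospital-level ones, to offset the fixed two-month implementation period. Additional file 6 is cited for the detailed statistical model, at the hospital-level analysis, and is not at hand.

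**The concern.** The GEE sandwich variance is justified as the number of clusters grows. With nine, two errors act in the same direction. The residuals used in the sandwich are too small because the fit has already been pulled towards each cluster, so the standard error is biased downwards. The normal quantile also ignores how variable that standard error is. Intervals come out too narrow and p-values too small.

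What is at stake is the department-level estimate of the bundle's effect, which is the analysis that uses the staggered start dates, and the stated objective of relating adherence to incidence. The model with all indicators combined is the most exposed. With one continuous indicator for each of the five measures, an intercept and two seasonal terms (assuming these carry over from the effectiveness model), it has 1 + 5 + 2 = 8 parameters on nine clusters. The Process indicators section allows more than one indicator per measure.

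**Working it through.** The article gives no error rate, power or sample size for these models, so there is no figure of its own to reproduce.

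**Inputs from the article.** Nine clusters; Poisson GEE with log link; baseline of at least 12 months, implementation of 2 months, intervention of at least 12 months; data from 2017 to the end of February 2020, at most 3 × 12 + 2 = 38 months if they start in January 2017.

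**Assumptions.** Two-sided 5% level; 1 to 2 cases per 1000 patient days; 500 to 2000 patient days per department-month; between-department SD of the log rate 0 to 0.5; autoregressive monthly noise with SD 0 to 0.3 and correlation 0 to 0.7. In one scenario the department-specific effect varies with SD 0.2 around zero.

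**Step 1, reference distribution alone.** If the standard error were unbiased but carried only 8 df, the true level of a z-test would be P(|t₈| > 1.96) = 8.6%. With 4 df (9 clusters minus 5 coefficients) it would be 12.2%.

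**Step 2, simulation under no average effect.** The model has five coefficients: intercept, implementation, intervention, sine and cosine. There were 1,500 runs per scenario, so the Monte Carlo SE is √(0.12 × 0.88 / 1500) ≈ 0.8 points. The sandwich is B (Σ gᵢgᵢ′) B with gᵢ = Dᵢ′Vᵢ⁻¹eᵢ. Mancl-DeRouen replaces eᵢ by (I − Hᵢ)⁻¹eᵢ, where Hᵢ = DᵢBDᵢ′Vᵢ⁻¹. The SE ratio is the mean sandwich SE over the true SD of the estimate.

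| Months | Rate | Dept SD | Noise SD, corr. | Effect SD | Working corr. | Sandwich, z | Mancl-DeRouen, t(8) | Model-based, z | SE ratio |
|---|---|---|---|---|---|---|---|---|---|
| 38 | 1 | 0.3 | 0.3, 0.5 | 0 | independence | 13.5% | 5.5% | 9.2% | 0.83 |
| 38 | 1 | 0.3 | 0.3, 0.5 | 0 | exchangeable | 12.9% | 5.9% | 8.1% | 0.84 |
| 38 | 1 | 0.3 | 0.3, 0.5 | 0 | AR(1) | 13.7% | 5.5% | 5.7% | 0.83 |
| 38 | 1 | 0 | 0, 0 | 0 | AR(1) | 11.5% | 4.5% | 5.7% | 0.90 |
| 38 | 2 | 0.5 | 0.3, 0.7 | 0 | AR(1) | 12.3% | 4.5% | 2.8% | 0.87 |
| 38 | 2 | 0.5 | 0.3, 0.7 | 0 | exchangeable | 11.7% | 4.8% | 14.7% | 0.91 |
| 38 | 1 | 0.3 | 0.3, 0.5 | 0.2 | AR(1) | 10.9% | 4.1% | 9.7% | 0.88 |
| 32 | 1 | 0.3 | 0.3, 0.5 | 0 | AR(1) | 12.2% | 5.1% | 5.1% | 0.86 |
| 26 | 1 | 0.3 | 0.3, 0.5 | 0 | AR(1) | 11.8% | 4.4% | 4.4% | 0.88 |

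Neither half of the correction is enough alone. Mancl-DeRouen with z gives 6.9% to 9.3%, and the uncorrected sandwich with t(8) gives 6.5% to 8.7%.

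**Step 3, other settings.** A separate simulation assumed 38 months, 2 cases per department-month, between-department SD 0.3 and shift SD 0 to 0.2. With AR(1) it gave 11.1% uncorrected against 4.7% corrected (5,815 runs). With exchangeable or independence structures it gave 8.5% to 11.2% against 3.8% to 4.2% (400 runs each, Monte Carlo SE about 1.5 points). A third gave 9% to 13.5% against 2% to 6%. Together, the uncorrected test runs at about 9% to 14%.

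**Step 4, process indicators.** With indicators unrelated to outcome (400 runs per setting, 38 months, 2 cases per department-month, exchangeable correlation), a single indicator was falsely flagged in 17% of runs by the robust z-test, against 5% with Mancl-DeRouen and t(8). With five indicators together, each was flagged in 18% against 4%, and the uncorrected joint Wald test rejected in 67%.

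**The case against.** The strongest reply is that this argues from silence in a condensed article. The article never says that an uncorrected sandwich or a normal reference will be used and sets no 5% level, and variance detail may sit in Additional file 6 or an analysis plan. That stands as a limit on the claim: the 9% to 14% belongs to the usual way of running the stated model, not to anything the plan commits to. It does not remove the point, because the article itself fixes nine clusters for these models and their usual form gives intervals that are too narrow.

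A second reply is that model-based standard errors with the autoregressive structure, which the article offers as its example, ran at 2.8% to 5.7%. That is correct for a common effect. The article gives that structure only as an example; with independence or exchangeable correlation the rate was 8.1% to 14.7%. It was 9.7% when effects varied by department, and 14.5% to 20% in the third simulation. Variation is what the design leads one to expect: departments adapt delivery locally, and the Fig. 1 legend foresees differing degrees of success.

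Three stronger readings are tempting and are not supported:

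- *That every interval is too optimistic.* The hospital-level Poisson analysis does not use departments as clusters, and the GEE result depends on choices the article does not state.
- *That the eight-parameter sandwich is rank-deficient.* The cluster scores sum to zero, so its rank is at most 8, which can still be full rank for 8 parameters. Only a ninth would force singularity.
- *That fewer than nine departments are independent.* The phrase "departments sharing same nursing or medical personnel" is an example under one of four selection criteria. The article does not say how many departments share staff or that their counts are correlated as a result.

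**Conclusion.** The concern holds in conditional form. The nine-cluster GEEs, for department-level effectiveness and for the process indicators, need a small-sample correction, and the article states none. Run with the default robust z-test, the effectiveness GEE would reject a true null in about 9% to 14% of trials at an assumed 5% level. In the main simulation the mean standard error was 0.83 to 0.91 of its true value, so intervals would be about 9% to 17% too narrow even before the gap between z and t is counted. These figures rest on assumed event rates, patient days, variance components and study length, though the direction was the same in every scenario tried, including pure Poisson data (11.5%). It would go too far to infer that the primary-outcome result as a whole is compromised, since one of the two effectiveness analyses is untouched.

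**What to change.** State that all GEEs, for effectiveness and for process indicators, use bias-corrected robust standard errors (for example Mancl-DeRouen) with a t reference on 8 df, the number of clusters minus one. Both parts must be named, since neither alone restores the level. Base inference on the process indicators on the single-indicator and adherence-score models already planned, and present the all-indicators models as descriptive, because the continuous version has at least 8 parameters on nine clusters.

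The work is an analysis option and one sentence. The real cost is width. The quantile ratio is 2.306 / 1.96 = 1.177. If the corrected standard error is about right on average, intervals grow by a factor between 1.177 / 0.91 = 1.29 and 1.177 / 0.83 = 1.42, so roughly 30% to 40% wider than the default ones, with a matching loss of apparent precision.

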The limitations of our study are the following: First, our study does not include a control group. We abstained from conducting a randomized controlled trial due to anticipated high contamination between departments/wards within the same hospital. Second, the duration of the implementation period is determined to be 2 months not accounting for possibly longer duration due to the formative approach of the implementation strategy. We aim to address this point by analysing the results both on the hospital and department level. Third, by continuously collecting process indicators from EMR, we cannot preclude reporting bias (e.g. increased documentation of oral care). We address this issue by additionally measuring process indicators on an individual basis. Further, although we take efforts to demonstrate empathic neutrality during our qualitative data collection, we cannot entirely preclude the possibility that qualitative researchers may be perceived as being partial, leading to potential desirability bias in the qualitative data. Finally, we acknowledge that our formative process evaluation does in itself lead to changes in implementation plans and that these changes must be documented with great care to keep track of the exact implementation activities. Rather than purely a limitation, we view this as a strength of our study, and we anticipate that it should also be integrated into recommendations for those wishing to replicate results of our future nvHAP study.

In conclusion, with this innovative mixed-methods study design, we will assess the effectiveness of the nvHAP bundle, but also measure process indicators of the nvHAP bundle and contextual factors influencing implementation uptake. We will be able to triangulate our findings, i.e. correlate nvHAP rates with adherence data of the prevention bundle and again with qualitative measures of implementation success. Further, our mixed-method approach will be of great value to understanding the complex contextual interactions that influence implementation success, which are necessary to inform implementation guidance for other institutions planning to implement the nvHAP bundle.

Addendum: Due to the COVID-19 pandemic, the study data collection had to be terminated earlier than planned (i.e. end of February 2020). Additional file 7 informs about the details of early study termination.

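### Neither effectiveness model has a calendar-time term, so in this study without a control group a non-seasonal change in the nvHAP rate is confounded with the bundle effect

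*Protocol article*

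**What the plan says.** The section on analyses of nvHAP bundle effectiveness describes two models.

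- **Hospital level.** A Poisson regression of the monthly total, in which "a change point model will be combined with piecewise constant rates with additional sine-cosine waves to account for seasonality". The explanatory variable is the period: "Study period on the hospital level (hospital baseline, implementation, intervention period) will be used as explanatory factor".
- **Department level.** A Poisson GEE with departments as clusters: "We will use a time-dependent, department-specific binary indicator variable for department-level implementation of the intervention bundle", possibly with an intermediate level for the implementation phase. The only other adjustment named is for season: "Further, we will adjust for seasonality of nvHAP incidences by inclusion of sine/cosine waves". Serial dependence is handled through the working correlation, with a first-order autoregressive structure as the example.

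One sensitivity analysis drops 2017, to look for regression to the mean after departments were chosen partly on their 2017 rates. Among the limitations, the Discussion states that "our study does not include a control group" and explains why. It does not mention secular trend.

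**The concern.** In an uncontrolled before-after comparison, the period contrast measures the bundle effect multiplied by whatever else changed between the periods. Annual waves repeat each year, so they cannot follow a drift across years in, for example, case mix, imaging practice or staffing. If the rate was already falling, the models would credit the fall to the bundle. If it was rising, they would hide a real benefit. The first objective is the effect of the bundle on the incidence rate, which is also the primary outcome, so the main conclusion depends on an assumption of no drift that the article neither states nor checks. The design offers a partial remedy: each department chooses its own start, so at department level bundle exposure and calendar time are not the same variable.

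**Working it through.** The article states no sample size, power or effect size, so there is no figure to reproduce. The check asks what the two models return when the bundle does nothing and the background rate drifts.

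**From the article:** the two mean structures above; nine departments; baseline of at least 12 months, implementation of 2 months, intervention of 12 months or longer; department-chosen starts; data collection ended in February 2020.

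**Assumed:** data from January 2017, hence 38 months; starts in months 14, 16, 17, 18, 19, 20, 21, 22 and 24, counted from zero; a constant yearly percentage drift; a moderate annual cycle; equal department sizes; independence working correlation in the GEE.

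**Step 1, hand check at hospital level.** Baseline covers months 0 to 13 (midpoint 6.5). Intervention covers months 26 to 37 (midpoint 31.5). The gap is 25 months, or 25/12 = 2.08 years, and the spurious rate ratio is about (1 − yearly decline)^2.08:

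- 5% decline: 0.95^2.08 = 0.90
- 10% decline: 0.90^2.08 = 0.80
- 15% decline: 0.85^2.08 = 0.71

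**Step 2, both models fitted to expected counts with a true rate ratio of 1.**

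| Drift per year | Hospital model | Department model | Either model plus linear time |
|---|---|---|---|
| −5% | 0.90 | 0.92 | 1.00 |
| −10% | 0.80 | 0.84 | 1.00 |
| −15% | 0.71 | 0.77 | 1.00 |
| +10% | 1.22 | 1.17 | 1.00 |

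The staggered starts dilute the bias at department level but do not remove it.

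**Step 3, shortest design.** With 12 + 2 + 12 months and all departments starting together, the midpoints are 14 months apart: 0.95^(14/12) = 0.94, 0.90^(14/12) = 0.88, 0.85^(14/12) = 0.83. The fitted values are 0.94, 0.88 and 0.82 in both models, so the bias does not depend on the assumed 38 months.

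**Step 4, false-positive rate of the hospital model** (500 simulations, nominal two-sided 5%, 20 assumed cases per month): 0.03 with no drift, and 0.22, 0.64 and 0.94 at declines of 5%, 10% and 15%. With a time term it stays between 0.03 and 0.06. At 10 to 40 cases per month, the 10% decline gives 0.35 to 0.93.

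**Step 5, the planned safeguards.** Annual waves are in every fit above. The autoregressive option concerns correlation and weighting and puts no trend in the mean. Dropping 2017 at a 10% decline moves the department-level ratio from 0.84 to about 0.9, still short of 1.

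**Step 6, cost of a time term.** The standard error of the log rate ratio rises 1.6- to 2.1-fold in the department model with staggered starts, and about 2.8-fold if all start together. In the hospital model it rises 2.2- to 3.8-fold, because period and time are nearly collinear there.

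**The case against.** **The article is condensed.** Its detailed statistical model is in Additional file 6, which is not shown. A trend in the hospital model would contradict the stated piecewise constant rates. The department model is described less completely (no patient-day offset is named for it), so a missing term is weaker evidence there. This limits certainty, but the article lists that model's explanatory variable and its further adjustment, and time is in neither.

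**No trend is documented.** This stands. The yearly drifts are assumptions, and the rate ratios and false-positive rates hold only under them.

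**A time term can mislead too.** This also stands. The implementation strategy is formative, and the Discussion concedes that implementation may take longer than two months. Suppose there is no drift and the benefit grows to a rate ratio of 0.70 over 12 months (assumed). The department model then gives about 0.76 to 0.77 without time and about 0.84 to 0.87 with linear time, depending on how the ramp is laid out. The time-adjusted estimate should therefore not replace the planned one.

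**Comparison series.** A reader might infer, because departments were selected on "nvHAP rate above the 50th percentile according to UHZ nvHAP data from the year 2017", that non-selected departments offer an unused comparison series. The article shows only that 2017 rates existed, and that year is baseline. It does not show that surveillance continued there, and it expects contamination within the hospital. That is no omission in the plan.

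**Conclusion.** The point holds: as described, both effectiveness models confound the bundle with any non-seasonal change in the background rate, and no planned analysis removes this. Under the assumptions listed, with no bundle effect, declines of 5% to 15% per year produce department-level rate ratios of about 0.92 to 0.77 and hospital-level ratios of about 0.90 to 0.71. A 10% yearly rise would mask benefit to a similar degree.

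Two stronger readings are not supported. One is that every background change is counted as a bundle effect; annual cycles are modelled, so only non-seasonal change is at issue. The other is that the first objective cannot be answered at all; it can be answered if drift is absent, and the article contains no evidence either way. What is missing is a prespecified analysis that does not rest on that assumption.

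**What to change.** Prespecify a second version of the department-level GEE with calendar time added, linear in months, with a spline as a check. Report it beside the planned model without time. State in advance what counts as agreement between the two. Attribute a rate change to the bundle only if the time-adjusted estimate is consistent with it; otherwise describe the result as a before-after change that may reflect secular trend. The hospital-level model can stay as a descriptive summary, since adjustment for time is expensive there.

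The change is one covariate and needs no new data, so the early end of data collection does not prevent it. The price is precision. With about 18 cases per month (assumed: nine departments × 1,333 patient-days × 1.5 per 1000), the standard error goes from about 0.08 to about 0.16. A 95% interval around a rate ratio of 1 then widens from exp(±1.96 × 0.08) = 0.85 to 1.17 to exp(±1.96 × 0.16) = 0.73 to 1.37. The linear term may also absorb part of a slowly building effect, which is why both estimates should be shown.
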